## Abstract

**Background:**

The relevance of regular moderate to intense exercise for ameliorating psychomotor symptoms in persons with multiple sclerosis (pwMS) is becoming increasingly evident. Over the last two decades, emerging evidence from clinical studies and animal models indicate immune regulatory mechanisms in both periphery and the central nervous system that may underlie these beneficial effects. The integrity of the blood-brain barrier as the main structural interface between periphery and brain seems to play an important role in MS. Reducing the secretion of proteolytic matrix metalloproteinases (MMP), i.e. MMP-2, as disruptors of blood-brain barrier integrity could have profound implications for MS.

**Methods:**

In this two-armed randomized controlled trial 64 participants with relapsing-remitting MS (RRMS) (EDSS 0–4.0) will be allocated to either an intervention group or a passive wait list control group. The intervention group will perform 60 min of combined functional resistance and endurance exercises 3x per week over a period of 12 weeks in a community-based and publicly available setting. Changes in serum concentration of MMP-2 will be the primary outcome. Secondary outcomes are numbers of immune cell subsets, soluble (anti-) inflammatory factors, physical capacity, cognitive performance, physical activity behavior, gait performance, and patient-reported outcomes. All outcome measures will be assessed at baseline and after week 12 with an additional blood sampling before, during and immediately after a single training session in week 6.

**Discussion:**

To our knowledge, this will be the first RCT to investigate both the acute and chronic effects of a community-based intense functional resistance and endurance exercise regimen in persons with RRMS. Combining analysis of biological and cognitive or psychological outcomes may provide a better understanding of the MS-specific symptomology.

**Trial registration:**

DRKS00017091; 05th of April, 2019; International Clinical Trials Registry Platform.

## Background

Accumulating evidence over the past two decades underlines the role of a dysregulated immune system in the pathophysiology and progression of multiple sclerosis (MS) [1]. The broad immunoregulatory effects of regular exercise is becoming more evident and is now recommended as an adjunct therapy for people suffering from chronic (neuro-)inflammatory diseases, such as MS [2–4]. Evidence-informed physical activity guidelines for persons with MS (pwMS) have already been developed [5], but less than 30% of pwMS meet the recommended guidelines for moderate to vigorous exercise [6]. A perturbed peripheral immune homeostasis indicated by the imbalance of T cell subsets seems to be a major disease-specific characteristic [7, 8]. Interestingly, there might be a proposed intensity-dependent effect of physical exercise on regulatory T cell homeostasis by increasing their cell counts and anti-inflammatory potential [9].

Moreover, there are emerging biopsychosocial models that link a dysregulated immune system, i.e. proinflammatory cytokines, to cognitive impairment and fatigue which represent the most relevant symptoms for pwMS [10, 11]. It was shown in different patient cohorts that exercise might be a promising therapeutic approach to improve cognitive performance [12–14] with both resistance and endurance exercise being feasible and beneficial for pwMS [15, 16].

The classification of MS as an autoimmune neuroinflammatory disease favored research to elucidate how activated peripheral (autoreactive) immune cells or neurotoxic substances invade into the central nervous system (CNS) and contribute to disease progression. Increased secretion of proteolytic matrix metalloproteinases (MMP), i.e. MMP-2, as modulators of blood-brain barrier (BBB) integrity seems to have profound implications for MS [17–19]. We have shown that, in contrast to moderate continuous training, high intensity interval training over a period of 3 weeks reduces serum levels of MMP-2 [20]. Further, a recent systematic review of human intervention studies concludes that exercise training positively modulates BBB permeability markers in pwMS [21].

Acute intense exercise provokes a transient inflammatory state and enzymatic conversion of tryptophan (TRP) to kynurenine (KYN) and further KYN metabolites ( [22], Joisten 2019 accepted). It is assumed that exercise-induced activation of immune cells plays a significant role in this process. KYN may has potent immune regulatory characteristics by inhibiting the activation of pro-inflammatory immune cells while promoting differentiation of regulatory T cells [23, 24]. However, chronic synthesis of KYN through long term peripheral immune dysregulation seems to be involved into the pathophysiology of MS [25, 26]. By passing the BBB, KYN can be metabolized into neurotoxic quinolinic acid (QUIN) by locally activated immune cells. Exercise-induced conversion of KYN to kynurenic acid (KYNA) and NAD+ may decrease translocation of KYN into CNS, thereby limiting kynurenine-associated neurotoxicity [27, 28].

In a review discussing the relevance of immune regulatory treatments in MS, Dendrou et al. [1] recommend multimodal targeting of peripheral and CNS-intrinsic inflammation in early disease stages. Further, Riemenschneider et al. [29] propose to conduct exercise treatments in the early disease stage to promote evidence-based clinical integration for a “window of opportunity” in MS exercise therapy.

Since opportunities for early-phase MS rehabilitation in rehabilitation centers are rare and limited to some weeks per year, the overall objective of this study is to investigate the chronic effects of a community-based 12-week exercise training in a publicly available setting in pwMS with light symptomatology. By correlating the assessed cognitive capacity and patient-reported outcomes like anxiety/depression and fatigue with immune-related biomarkers and cell populations, existing hypothetical biopsychosocial models in pwMS [10] will be addressed in the context of exercise neuroimmunology.

## Methods/design

In this study, a two-armed single-blind randomized controlled trial design will be applied. Prior to (T_0_) and 48 h after the intervention period (T_2_), an assessment of cardiovascular fitness, muscular strength, cognitive performance, gait performance and patient-reported outcomes (depression and anxiety, fatigue, quality of life, sleep quality, physical activity behavior, social integration) will be conducted. Blood samples at rest will be taken at T_0_, midpoint (T_1_) and T_2_. To investigate acute changes of BBB markers, immune homeostasis, (anti-) inflammatory factors as well as TRP metabolites, there will be an additional assessment of blood samples before (T_1_), during (T_1.1_) and after (T_1.2_) a training session with the resting values at T_1_ being further used for midpoint follow-up. Blood samples from the control group at T_1_ will be assessed without further measurements at T_1.1_ and T_1.2_. To control for the participants’ daily activity level, the participants will be asked to adhere to a 7-day actigraphic measurement on three time-points (T_0_,T_1_,T_2_).

All assessments and blood-sampling will be conducted at the German Sport University Cologne, except for the blood samples at T_1_,T_1.1_,T_1.2_ in the intervention group. This blood sampling will be done by a physician at the fitness center.

Due to the nature of the trial, participants could not be blinded to group allocation. Assessors taking outcome measures post intervention will be blinded to group allocation. The training sessions will be supervised by MS experienced exercise scientists. The trainers will not be involved in the post assessment to keep blinding.

### Participants and recruitment

A total of 64 persons with definite diagnosis of relapsing-remitting multiple sclerosis (RRMS) (revised McDonald criteria [30]) will be recruited through announcements at the German Sports University Cologne, the Deutsche Multiple Sklerose Gesellschaft (DMSG, Ortsvereinigung Köln und Umgebung e.V.), and local MS clinics. The participants will be screened for eligibility by the study supervisor with further key inclusion criteria of an Expanded Disability Status Scale (EDSS) [31] score between 0 and 4.0.

### Eligibility

Prior to inclusion, participants will be screened for exclusion criteria and general sports capability (see Table 1). If eligible, the participant will be asked to provide written informed consent. After stratification, the participants will be randomized to either the intervention group or a passive waitlist control group.

**Table 1 Tab1:** Detailed list for eligibility screening

Inclusion criteria	Exclusion criteria
♦ *Age: 18–45 years*	♦ *Acute episode or significant exacerbation of multiple sclerosis symptoms during intervention*
♦ *EDSS: 0–4.0 (inclusive)*	
♦ *Approved sport capability*	
♦ *Approved RRMS*	♦ *Cardiac preload*
	♦ *Orthopaedic diseases limiting the execution of the intervention and assessments*
	♦ *Problems in understanding (not German-speaking)*
	♦ *Concomitant disease states (internistic or neurological) affecting study outcomes*
	♦ *Cancer diseases under treatment of chemotherapy or radiation therapy*
	♦ *Pregnant or breast-feeding women*

*EDSS* Expanded Disability Status Scale, *RRMS* Relapsing-remitting multiple sclerosis

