### Study intervention

#### Experimental intervention group

All training sessions will take place in a publicly available fitness center in Cologne, Germany. Participants of the intervention group will conduct three training sessions per week for a period of 12 weeks. In groups of maximal ten, the participants will perform endurance and resistance exercises for 60 min with 30 min of resistance exercises and 20 min of endurance/ strength endurance exercises. Each session will be supervised by MS experienced exercise scientists. To guarantee appropriate muscle activation, a 10-min warm-up with light aerobic activity and mobilization will be applied. An additional table shows the exercise program in more detail (see Additional file 1). To avoid difficulties with fixed-time training sessions and to improve adherence, participants will be able to choose between different weekdays and time slots.

A progressive periodization with step by step learning will be applied during the first 2 weeks of the intervention to guarantee precise movement execution of free weight resistance exercises. Thereafter, the participants will increase the load in consultation with the trainer.

The endurance / strength-endurance part comprises alternating short ergometer exercises, body weight exercises and exercises with small, functional devices (e.g. medicine ball or kettlebell) with rest periods of at least 1 min after each exercise. The exercises follow the principle “as much repetitions as possible”. The workload will be increased from 4 × 2 min to 4 × 3 min to 4 × 4 min according to the performance level of the participants.

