**Fig. 1 Fig1:**
[figure not shown]
Flow diagram of this study. Baseline testing (T_0_) will be done before stratified randomization/allocation to either group. There will be a further collection of blood samples 6 weeks after intervention onset (midpoint) at rest (T_1_), after resistance exercises (T_1.1_) and immediately after the training session (T_1.2_) to investigate effects of acute training. Assessment of blood samples from the control group at T_1_ will be done at the German Sport University Cologne without further measurements at T_1.1_ and T_1.2_. After the 12-week intervention period (T_2_), all outcome measures will be assessed 48 h after the last training session to investigate effects of chronic training

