### Primary analysis

An intention-to-treat analysis will be conducted. To investigate the effect of the intervention (12-week exercise intervention of combined functional resistance and endurance exercise) compared to control on the primary outcome MMP-2, we will conduct a 2 (intervention group vs. control group) × 2 (T_0_ vs. T_2_) analysis of covariance (ANCOVA). This model will be adjusted for baseline values and lean body mass at T_0_. As measure of effect size partial Eta-squared and Cohen’s d values, respectively, will be calculated.

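### Table 1 lists an MS relapse during the intervention as an exclusion criterion, which permits exclusion after randomisation and conflicts with the stated intention-to-treat analysis

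*Protocol article*

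**What the plan says.** The Eligibility section of the protocol article states: "Prior to inclusion, participants will be screened for exclusion criteria and general sports capability". It refers to Table 1, whose caption presents it as the list for eligibility screening. The first entry in the exclusion column is "Acute episode or significant exacerbation of multiple sclerosis symptoms during intervention" (called relapse below). The section then goes on to consent and allocation: "After stratification, the participants will be randomized to either the intervention group or a passive waitlist control group".

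The caption of Fig. 1 confirms the order, since baseline testing (T0) "will be done before stratified randomization/allocation to either group". The Experimental intervention group section says that participants in that arm "will conduct three training sessions per week for a period of 12 weeks".

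On who is analysed, the Primary analysis section says "An intention-to-treat analysis will be conducted", and the Secondary analysis section opens with the same sentence. Neither says more about the analysis set.

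Two further statements bear on the consequences. Methods/design notes that "participants could not be blinded to group allocation". The Background describes matrix metalloproteinases, MMP-2 among them, "as modulators of blood-brain barrier (BBB) integrity seems to have profound implications for MS".

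**The concern.** A criterion that nobody can meet at screening cannot work as a screening criterion. Its only practical effect is to make a randomised participant excludable because of something that happened after randomisation. Intention-to-treat requires that everyone randomised is analysed in the allocated arm. If exclusion means leaving the study, both statements cannot be followed.

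The comparison of MMP-2 from T0 to T2, and the secondary comparisons with it, would then rest on participants selected by their disease course under treatment and no longer on the groups formed by randomisation. Even if nobody intends this, two teams working from the same text could build different analysis sets.

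**Working it through.** The point is one of logic, and no figure in the plan is at issue.

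**Step 1: the order of events.**

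| Event | Where stated | Relative to randomisation |
|---|---|---|
| Screening against Table 1 | Eligibility | before |
| Consent | Eligibility | before |
| Baseline testing T0 | Fig. 1 caption | before |
| Allocation | Eligibility; Randomization | – |
| 12-week intervention period | Experimental intervention group | after |
| Relapse during the intervention | Table 1, exclusion column | after |

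The last row is a screening criterion that can be met only after allocation. No section limits it to stopping training, and none says that participants who meet it stay in follow-up.

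**Step 2: when exclusion would bias the comparison.** Let p_E and p_C be the shares relapsing in the exercise and control arms, and d the shift in MMP-2 at T2 caused by a relapse (in SD, equal in both arms). Let q_E and q_C be the shares of relapses detected and excluded, and t the between-arm difference (exercise minus control) apart from relapse. Assume that participants who relapse otherwise resemble the rest.

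- All randomised: t + (p_E − p_C) × d
- After exclusion: t + [p_E(1 − q_E)/(1 − p_E q_E) − p_C(1 − q_C)/(1 − p_C q_C)] × d

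Three cases follow.

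- *Equal p and equal q*: both expressions reduce to t, so this mechanism gives no bias.
- *Unequal p, all relapses excluded (q = 1 in both arms)*: the part (p_E − p_C) × d is lost. With assumed shares of 5% and 10% and an assumed d of 0.5 to 1.0 SD, that part is (0.05 − 0.10) × 0.5 = −0.025 to (0.05 − 0.10) × 1.0 = −0.05 SD. Exclusion would here hide a benefit of exercise.
- *Equal p, q_E larger than q_C*: fewer relapsers remain in the exercise arm. If d is positive, the result is shifted in favour of exercise.

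The sign can therefore go either way. The documents supply none of p, q or d.

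**Step 3: could detection differ?** The exercise arm has 3 × 12 = 36 planned supervised sessions, and the Data management section adds a call or email after two consecutive missed sessions. For controls after allocation, the article describes study contact at T1 and T2. Participants know their allocation, so symptom reporting may also depend on the arm. This makes unequal detection plausible but does not show it.

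**Step 4: how many participants (assumed rates only).** With a constant rate L per person-year, the share relapsing in 12 weeks is 1 − exp(−L × 12/52).

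- L = 0.1: 2.3%, and 64 × 0.0228 = 1.5 participants
- L = 0.2: 4.5%, and 64 × 0.0451 = 2.9 participants
- L = 0.5: 10.9%, and 64 × 0.109 = 7.0 participants

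**The case against.** The strongest reply is that the article never says a relapsing participant is dropped from follow-up or analysis. The entry may be a loosely worded screening item, or a rule on stopping training that ended up in the wrong table. Stopping training is compatible with intention-to-treat, and intention-to-treat is the only statement in the article about who is analysed. A fuller protocol or an analysis plan may define the set.

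This stands in part: the text permits exclusion from the analysis but does not announce it. It does not remove the point, which rests on what Table 1 states and not on a missing detail. The entry contradicts the stated timing of screening on any reading.

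Three stronger readings are tempting but are not supported.

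- A reader might infer that the criterion applies to the exercise arm alone. The article, however, uses the intervention as a calendar period for both arms: Methods/design places T2 48 hours after that period, and the captions of Figs. 1 and 2 place T1, which is sampled in controls too, six weeks after its onset.
- A reader might infer that serum MMP-2 is expected to move in a relapse. The Background links MMP-2 to blood-brain barrier integrity in MS, but no section says that serum levels change during a relapse.
- A reader might want to express the bias as a share of the planned effect. That would need assumed values for every input and removal from one arm only. With equal relapse rates, shifts and removal in both arms, it is zero.

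**Conclusion.** Wrong as written. A criterion that can be met only after randomisation stands in a list to be applied before inclusion. It permits exclusion on a disease event in a trial that promises intention-to-treat for its primary and secondary outcomes. This conclusion needs no numerical assumption.

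The effect on the result is of unknown size and direction. It arises only if the criterion is used to remove participants from follow-up or analysis, and, on the simple model above, only if relapse or its detection differs between the arms. The 1.5 to 7 participants are for orientation and rest on assumed relapse rates.

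**What to change.** Reconcile the Eligibility section and Table 1 with the Primary and Secondary analysis sections.

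1. Keep in Table 1 only criteria that can be assessed before randomisation.
2. If an on-study relapse rule is intended, move it out of Table 1 and label it as affecting training only. Its content is for the clinical lead and is not judged here. Simply deleting the entry could remove a rule that was meant for participants in training.
3. State that all randomised participants, including those who relapse, are invited to T1 and T2 and are analysed as allocated.
4. Record relapse by the same method in both arms.
5. Optionally, add a sensitivity analysis that leaves out samples taken during a relapse, by the same rule in both arms.

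The cost is a rewording of one table entry, a sentence or two in the analysis sections, one relapse question at T1 and T2, and slightly more outcome variance.

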### Randomization

Participants will be randomly allocated (1:1) to either the intervention group or a passive waitlist control group. A concealed randomization approach will be conducted by an independent employee using “Randomization-In-Treatment-Arms” software (RITA, Evident, Germany) that follows the minimization procedure [32]. To ensure equal allocation of subgroups of participants to both experimental conditions, following stratification factors will be used: age, lean body mass, disease severity (EDSS), intake of immune regulatory medication, the sum of the hypothetical one-repetition maximums (h1RM_sum_) and peak power output (Watt_max_).

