### Assessment of physical capacity

To assess body composition of the participants, bioelectrical impedance analysis will be used and recorded according to the manufacturer’s instructions. The calculated lean body mass will be used as a stratification factor for randomization, since visceral adipose tissue has been described to play a significant role in inflammatory signalling [37] and therefore, may impact biological outcome measures.

Cardiorespiratory fitness will be assessed on a cycle ergometer (Ergoline®, Bitz, Germany) with a progressive cardiopulmonary exercise test (CPET). Participants will begin the test at an initial intensity of 30 W (one-minute warm-up), increasing by 15 W every minute until volitional exhaustion. This will be followed by a three-minute cool-down. The resulting Watt_max_ at T_0_ will be used as a stratification factor for randomization. The individual cardiorespiratory fitness level will be monitored by direct and continuous measurements (breath by breath) of VO_2peak_ by ergospirometry (Cortex, MetaLyzer 3B-R2, Germany). Blood lactate will be measured before, immediately after and 3 min after the CPET via earlobe prick.

To assess muscular strength, a five-repetition maximum (5RM) test will be conducted for lower (leg press) and upper body compartments (chest press, lat pulldown). The American College of Sports Medicine (ACSM) guidelines will be applied to assess the 5RM [38]. These guidelines state that, firstly, the participants should warm up by completing several submaximal repetitions. Secondly, the 5RM will be determined within four trials with rest periods of 3 min between trials. Thirdly, an initial weight that is within the subject’s perceived capacity (~ 50–70% of capacity) will be chosen. Thereafter, the resistance will be progressively increased by 2.5-20 kg until the subject is not able to complete the selected repetition(s). All repetitions should be performed at the same speed of movement and range of motion to ensure consistency between trials. Lastly, the final weight lifted successfully as the absolute 5RM will be recorded.

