### Data analysis

Statistical analyses will be performed by a statistician blinded to treatment groups. Level of significance is set at *p* ≤ 0.05. All values will be presented in means ± standard deviation. Statistical analyses will be conducted using the actual SPSS Version® (IBM®, Armonk, NY, USA) and R.

The required sample size to evaluate the between-group effect of the intervention on the primary outcome (serum changes of MMP-2 from baseline (T_0_) to post (T_2_)) in an analysis of covariance model (ANCOVA) was estimated using G*Power 3.1.9.2 [55]. Serum concentration of MMP-2 at baseline (T_0_) will be used as covariate. Based on already published study results [20], a medium to large effect size (Cohens d = 0.6) was used for sample size calculation. Statistical significance will be set 5% with statistical power (1-β) of 0.8. The sample size was calculated according to the formula N = (1-r2)*n described by Borm et al. [56]. The correlation was conservatively set at r = 0.6 which results in a preliminary sample size of *N* = 58. The expected drop-out rate is 15%. Therefore, a total of 64 participants will be recruited.

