### Secondary analysis

An intention-to-treat analysis will be conducted. To investigate the effect of the intervention compared to control on secondary outcomes, a baseline-adjusted 2 (intervention group vs. control group) × 2 (T_0_ vs. T_2_) ANCOVA model will be applied. To determine if groups differ at T_1_ and/or at T_2_, simple effects analyses (Bonferroni corrected) will be performed.

As measure of effect size partial Eta-squared and Cohen’s d values, respectively, will be calculated. Bivariate correlation analyses (Pearson) will be conducted to determine potential associations between changes in biomarkers and physical performance outcomes, cognitive performance and/or patient-reported outcomes from T_0_ to T_2_ (delta T_2_-T_0_).

To investigate the effect of an acute training session on biological markers in intervention group participants, we will conduct a repeated measures ANOVA at T_1_ (baseline), T_1.1_ (during) and T_1.2_ (post) exercise session.

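### Six factors drive the minimisation, but the primary model keeps one and most secondary models none: conservative and less powerful to the extent that the omitted factors are prognostic

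*Protocol article*

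**What the plan says.** The Randomization section describes 1:1 allocation by minimisation. It lists four balancing factors, "following stratification factors will be used: age, lean body mass, disease severity (EDSS), intake of immune regulatory medication", and then two more, "the sum of the hypothetical one-repetition maximums (h1RM_sum_) and peak power output (Watt_max".

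The Primary analysis section fixes the covariates for MMP-2: "This model will be adjusted for baseline values and lean body mass at T_0". The Data analysis section makes clear which baseline value is meant: "Serum concentration of MMP-2 at baseline (T_0_) will be used as covariate". One of the six factors is therefore in the primary model, and age, EDSS, medication, h1RM_sum and Watt_max are not.

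The Secondary analysis section plans "a baseline-adjusted 2 (intervention group vs. control group) × 2 (T_0_ vs. T_2_) ANCOVA model will be applied" and names no balancing factor.

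The section on physical capacity explains why lean body mass was made a factor: through its link with inflammatory signalling it "may impact biological outcome measures". No section explains why it alone is kept for MMP-2, or why it is dropped for the other biological outcomes.

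**The concern.** Minimisation makes the arms alike on the chosen factors. If such a factor predicts the outcome, balancing it removes part of the true variability of the treatment difference. A model that leaves the factor out still counts that part as residual noise. The reported standard error is then larger than the true one, the test runs below its nominal level, and the precision bought by the allocation is not used.

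The article does not leave the covariates open for an analysis plan to settle; it states them. It also departs from its own reasoning, because lean body mass is said to matter for biological outcomes yet is absent from the models for immune cells and soluble factors. At stake are some power in a small trial and confidence intervals wider than they need be.

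**Working it through.** **Inputs from the protocol article.** d = 0.6, alpha 5% (two-sided reproduces N), power 0.80, r = 0.6 for baseline MMP-2, N = 58, drop-out 15%, 64 recruited, and six minimisation factors.

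**Assumptions not in the documents.** R² is the share of the variance left after baseline that the five omitted factors explain, taken from 0 to 0.4. Minimisation is assumed to use median splits with a biased coin of 0.8, or to be deterministic.

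**Step 1: the plan's own figure.** A two-sample t-test with d = 0.6 needs 45 per arm, 90 in total. 90 × (1 − 0.6²) = 90 × 0.64 = 57.6, so 58. This reproduces. It credits only baseline MMP-2, so the omitted factors play no part in N.

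**Step 2: patients analysed.** 64 × 0.85 = 54.4, so 54. SE = √(4 × 0.64 / 54) = 0.218, and 0.6 / 0.218 = 2.76. With 54 − 4 = 50 degrees of freedom, power is about 0.77.

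**Step 3: size of the mechanism.** With perfect balance, the true variance of the difference is 4σ²(1 − R²)/N, while the planned model estimates 4σ²/N. The SE would be too large by 1/√(1 − R²): 1.05 at R² = 0.1, 1.12 at 0.2, 1.20 at 0.3. Balance on median splits is only partial for continuous factors, so the real excess is smaller.

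**Step 4: simulation.** 54 analysed, coin 0.8, 3,000 runs per row, outcome driven by the continuous factor values. The planned model has arm, baseline and lean body mass; the full model adds the other five factors.

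| R² | Planned: model SE / true SE | Planned: type I error | Power, planned | Power, full | Difference (points) |
|---|---|---|---|---|---|
| 0 | 0.220 / 0.224 | 5.4% | 75.7% | 73.1% | −2.6 |
| 0.1 | 0.220 / 0.213 | 4.1% | 76.3% | 77.3% | +1.0 |
| 0.2 | 0.220 / 0.207 | 3.1% | 77.0% | 82.9% | +5.9 |
| 0.3 | 0.220 / 0.207 | 3.3% | 76.7% | 86.2% | +9.5 |
| 0.4 | 0.220 / 0.197 | 2.8% | 78.4% | 90.4% | +12.0 |

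The SE is too large by 0.220/0.213 = 1.03 at R² = 0.1, 0.220/0.207 = 1.06 at 0.2 and 0.3, and 0.220/0.197 = 1.12 at 0.4. Monte Carlo error on a type I error near 4% is √(0.04 × 0.96 / 3000), about 0.4 points. The full model's type I error at 54 stays between 4.3% and 5.5%, with either coin.

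**Step 5: other settings.**
- Deterministic minimisation, 54 analysed: type I error 4.6%, 4.4% and 3.4% at R² = 0.1, 0.2 and 0.3; power differences +1.8, +6.7 and +9.5 points; −2.3 at R² = 0.
- 64 analysed, coin 0.8: −2.0 points at R² = 0, then +1.9, +4.4 and +7.8.
- 58 analysed, outcome driven by the binary-coded factors, coin 0.9: type I error 4.0%, 3.0% and 2.5%; power 80.7% to 82.3%, 82.0% to 87.6% and 82.2% to 89.6%; 78.6% to 77.6% at R² = 0.
- Strength, fitness and lean body mass correlated at an assumed 0.6, 54 analysed, R² = 0.2: power 78.6% to 81.8%, a gain of about 3 points.

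**The case against.** The strongest reply is that the loss is conditional. It arises only if the five factors predict follow-up MMP-2 after baseline MMP-2 and lean body mass, and the documents give no such correlation. A reader might infer that the planned standard errors are simply wrong, or that adjustment is free. Neither is supported: at R² = 0 the planned model shows no fault and the extra covariates cost about 2 to 3 points. At 54 analysed, R² = 0.05 still gave 75.5% with the planned model against 74.8% with all factors, so break-even lies between about 0.05 and 0.1. This part of the reply stands.

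The coding also matters. If the outcome follows the continuous values rather than the categories used for balancing, the conservatism shrinks; one such run gave 4.6% at R² = 0.2, others 3.1% to 4.4%. Correlated factors roughly halve the power gain. The effect becomes smaller but keeps its direction.

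A reader might say that the secondary models adjust for no balancing factor at all. That is untrue for h1RM_sum, whose baseline is itself a factor, and for Watt_max and lean body mass if analysed as outcomes. A reader might also assume that medication and EDSS are the main drivers of immune markers. The documents do not say so, and eligibility limits EDSS to 0–4.0 and age to 18–45, which restricts what those two can explain.

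Finally, lean body mass has a stated rationale, and it is the factor kept for MMP-2. That explains its inclusion there. It does not explain leaving it out for the other biological outcomes.

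**Conclusion.** The mismatch between allocation and analysis is in the text and worth correcting, as a cheap improvement and not as a flaw that threatens validity. Any error is on the safe side: the planned test is conservative where the omitted factors are prognostic. A reader who infers a raised false-positive risk, bias or an invalid sample size goes beyond the documents.

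For an assumed R² of 0.1 to 0.3, type I error of the planned primary model is about 2.5% to 4.6% across the settings with 54 or 58 analysed (the 2.5% comes from 58 with binary-coded factors). Adjustment gains about 1 to 10 points of power at 54 analysed, against a cost of about 2 to 3 points if R² is near 0. These figures rest on the assumed R², the assumed coding for minimisation and d = 0.6 with r = 0.6. They were computed for the primary model. The same mechanism applies to the secondary between-group models, but its size there was not calculated.

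**What to change.** State in the Primary and Secondary analysis sections that each between-group model includes the outcome's baseline value and the minimisation factors: age, lean body mass, EDSS, immune regulatory medication, h1RM_sum and Watt_max, with continuous factors entered as continuous. Where a factor is itself the outcome's baseline, enter it once. Keep the model with baseline and lean body mass as a sensitivity analysis. The acute-session repeated-measures ANOVA is within the intervention group and needs no change.

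The cost is a sentence or two and no new data, since all six factors must be known before allocation. The primary model spends up to five more degrees of freedom (50 to 45 at 54 analysed) and most secondary models six (51 to 45). If the factors turn out not to be prognostic, about 2 to 3 points of power are lost. The covariates should be named before outcome data are seen, because adding them later would be open to challenge.
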